##### On-road driving assessment (RDA)

2.2.1.4

A driving instructor and a therapist carry out this 45-min assessment in a dual-control driving school car. In order to limit variability linked to the geographical diversity of the rehabilitation centers, driving routes were standardized between centers to ensure that they were comparable in terms of the traffic and road situations encountered. This route standardization was established in accordance with recommendations certified by the HAS (Haute Autorité de Santé, 2016). The TRIP (Test Ride for Investigation Practical fitness to drive) observation grid and scoring system are detailed in the case report form. Quantified measures of driving performance are collected during the assessment (15 sub-scores and a total score out of 100). The professionals present in the vehicle fill in this grid jointly after the RDA. The main interest of this grid, and the reason for its choice in this study, lies in the relevance of the tactical and strategic compensation scores in relation to Michon’s (1985) model. These scores reflect the behavioral self-regulation mechanisms adopted by drivers in order to compensate for any cognitive disorders and guarantee homeostasis of the task difficulty as described in the TCI model. Following this assessment, professionals issue an opinion on the participant’s driving ability (favorable, unfavorable or reserved).

##### Multiprofessional synthesis

2.2.1.5

Professionals then work together to issue a joint opinion (favorable, unfavorable or reserved) on the participant’s driving ability, based on the assessments carried out.

##### Patient feedback session

2.2.1.6

Professionals communicate the multiprofessional opinion to the participant, if possible in the presence of one or more relatives. They then provide the participant with documents required for the approved doctor visit: list of approved doctors, multiprofessional evaluation report, medical questionnaire, cerfa 14880*02 and, if necessary, a tutorial on completing formalities with the French National Agency for Secure Documents (Agence Nationale des Titres Sécurisés, ANTS).

##### Approved doctor visit

2.2.1.7

Following the multiprofessional evaluation, participants then have to undergo a consultation with an approved doctor from their department. They then inform the study investigator of the opinion issued by the approved doctor (fitness, temporary fitness and/or with restriction(s), unfitness).

##### Participant support

2.2.1.8

In the event of a favorable opinion, professionals help the participant with administrative formalities (ANTS website, road safety education office in the event of changes to the driving cab). In the event of an unfavorable or reserved opinion, professionals propose solutions to the participant (driving restrictions, rehabilitation in a simulator or driving school, time lapse before a new assessment, alternatives to driving, etc.).

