#### Longitudinal study

2.2.2

Six and 12 months after deliberation of the approved doctor’s opinion, the study investigators of the rehabilitation centers will send questionnaires to each participant of the cross-sectional study in order to study the road risk prediction performance of the tools and professional opinions. These questionnaires can also be completed with the help of a third party or a therapist. They will aim to gather information about participants’ driving in the 6 and 12 months since the opinion on fitness to drive was delivered. The elements investigated will concern:- aberrant driving behavior with DBQ validated in French (Guého et al., 2014),- possible changes in driving habits with DHQ, based on the Canadian Jerome Driving Questionnaire (JDQ©), and- road risk (accident rate and perceived risk).

Six months after the approved doctor’s opinion, participants will also be asked to complete a questionnaire (support for resuming driving questionnaire) to assess the relevance of multiprofessional educational support aimed at encouraging them to resume driving or dissuading them from doing so. In order to limit participant drop-outs, if they do not respond within one month, a reminder is sent by their SMR referent, with a one-month response period and this procedure will be repeated a second time if no response is received after this deadline. After these two reminders, the SMR referent may also contact the participant by phone to ensure that the e-mails have been received. If the participant refuses or does not reply, the SMR referent sends a final e-mail to the participant to inform them that they will be excluded from the longitudinal study.

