##### Main criterion: concordance between professional assessments

2.3.1.1

To meet the main objective, the concordance of the results of the neuropsychological assessment, RDA and multiprofessional evaluation will be studied in pairs (agreement between professional assessments). Each professional involved in the study will give a “favorable,” “reserved” or “unfavorable” opinion based on their practice. Evaluation criteria will correspond to cross-tabulated numerical values of results from each assessment tool studied (neuropsychological assessment, RDA and multiprofessional evaluation). “Reserved” opinions indicating driving restrictions will initially be classified as “unfavorable,” so that the results can be expressed as a binary Favorable/Unfavorable variable for each assessment. The RDA results will also include the number of driving instructor interventions on pedals, steering wheel and other car controls, using categorical variables. The values *a*, *b*, *c* and *d* (Table 1) will be used to perform the concordance test detailed in the next section (“Statistical analysis”).

**Table 1 tab1:** Evaluation criterion of the main objective for contingency table.

		Assessment x_i_	
		Favorable	Unfavorable
Assessment x_ii_	Favorable	*a*	*b*
	Unfavorable	*c*	*d*

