##### Secondary criterion C: road risk performance metrics 6 and 12 months after deliberation of the approved doctor’s opinion

2.3.2.1

The predictive performance indicators of assessment tools, TRIP grid, and approved doctor’s opinion will be estimated in relation to the road risk perceived by participants 6 and 12 months after deliberation of the approved doctor’s opinion (cf. secondary criterion D). The patient will indicate the increase in road risk to road risk according to their perception, in the form of a ternary variable in response to the question “How would you assess your road risk”: (i) lower than before, (ii) identical to before, (iii) higher than before the brain injury. The condition evaluated will be absence of increased road risk perceived by participants 6 and 12 months after the approved doctor’s opinion (negative result), corresponding to the “favorable” modality for assessments carried out in rehabilitation centers (neuropsychological, RDA and multi-professional evaluation) and “fit” for the approved doctor’s opinion (Table 4).

**Table 4 tab4:** Confusion matrix.

		Reality: perceived increased road risk 6 and 12 months after the approved doctor’s opinion has been issued	
		No increased road risk	Increased road risk
Prediction: assessment x_i_	Favorable	Real negative (RN)	False negative (FN)
	Unfavorable	False positive (FP)	Real positive (RP)

The TRIP score will also be analyzed continuously (total adjusted score out of 100), in total and by sub-score.

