### PREVAC study limits

3.3

Brain injury criteria are not controlled in the study, lesion location, severity and extent were not identified, suggesting heterogeneous clinical profiles. In addition, the temporal distance of the lesion was collected but not delimited. Although cognitive sequelae may persist for many years after brain injury, they tend to diminish over time. What’s more, the temporal distance of the lesion favors the development of compensatory strategies.

These factors generate a diversity of cognitive-behavioral profiles that contribute to a lack of homogeneity in the population studied, complicating interpretation of the results. It could be difficult to identify the profiles most likely to resume driving, and the study’s conclusions would then not be applicable to the population as a whole. Secondary analysis with subgroup studies will be conducted to measure differences linked to the temporal distance of the lesion.

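### Criterion C sets the index opinion against perceived risk measured after support offered only to unfavorable or reserved cases, so Table 4 does not show predictive accuracy alone

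*Protocol article*

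**What the plan says.** Section 2.2.1.8 (Participant support) divides what happens next by the result. On one side, "In the event of a favorable opinion, professionals help the participant with administrative formalities". On the other, "In the event of an unfavorable or reserved opinion, professionals propose solutions to the participant". The examples given are driving restrictions and "rehabilitation in a simulator or driving school, time lapse before a new assessment, alternatives to driving", and the list is left open. The section does not say whether the opinion meant is the team's joint opinion or the approved doctor's.

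Section 2.3.1.1 states that reserved "opinions indicating driving restrictions will initially be classified as" unfavorable. Both groups that are offered this support are therefore test-positive, at least in the initial coding.

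Section 2.2.2 says the centers "will send questionnaires to each participant of the cross-sectional study in order to study the road risk prediction performance"; this is done 6 and 12 months after the approved doctor's opinion and covers both instruments and opinions. Section 2.3.2.1 fixes the comparison: "The predictive performance indicators of assessment tools, TRIP grid, and approved doctor’s opinion will be estimated in relation to the road risk perceived by participants". The answer options are "i) lower than before, (ii) identical to before, (iii) higher than before the brain injury".

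Table 4 labels an unfavorable opinion with no increased risk a false positive. Section 2.3.3 computes accuracy, sensitivity, specificity, PPV and NPV from the four cells. Section 3.2 would then regard assessments that correlate with perceived risk as good predictors of road risk.

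**The concern.** Between the index opinion and the outcome, participants are offered different management, and the offer depends on the index result. The support is meant to change driving or the risk attached to it. A participant who was correctly flagged, then trained or reassessed, and who reports no increased risk at month 6 or 12 has only one place to go in Table 4: the false-positive cell. The table cannot tell a wrong alarm from a right alarm that was acted on. Driving restrictions and alternatives to driving can work in the same way.

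Criterion C is the part of the study that is to say which assessments predict road risk, and sections 3.2 and 3.4.2 carry the conclusions toward practice, public policy and the training of approved doctors. If the figures mix the quality of an opinion with the effect of the support that follows it, an assessment can look poor because its warning was heeded. Criterion E looks at support, but through usefulness ratings, and is not linked to criterion C. The limits in section 3.3 do not mention the issue.

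**Working it through.** The article gives no expected sensitivity, specificity, prevalence of increased risk or uptake of support, so there is no planned figure to reproduce. The direction follows from Table 4 and the formulas in section 2.3.3. The sizes below rest on assumed inputs.

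**Direction, for the opinion that governs support.** Let a share r of the true positives (RP) lose their increased risk through support. Then RP' = RP(1 − r) and FP' = FP + r·RP, with FN and RN unchanged.

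- Sensitivity = RP'/(RP' + FN): falls.
- Specificity = RN/(RN + FP'): falls.
- PPV = RP'/(RP' + FP'): falls, because the denominator is constant.
- Accuracy = (RP' + RN)/N: falls.
- NPV = RN/(RN + FN): unchanged.

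**Size, assumed base.** N = 100 (the planned total), 40 with increased risk in the absence of support, sensitivity and specificity 0.70: RP 28, FN 12, FP 18, RN 42.

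| r | RP' | FP' | Sensitivity | Specificity | PPV | Accuracy | NPV |
|---|---|---|---|---|---|---|---|
| 0 | 28 | 18 | 28/40 = 0.70 | 42/60 = 0.70 | 28/46 = 0.61 | 0.70 | 42/54 = 0.78 |
| 10% | 25.2 | 20.8 | 25.2/37.2 = 0.68 | 42/62.8 = 0.67 | 25.2/46 = 0.55 | 0.67 | 0.78 |
| 25% | 21 | 25 | 21/33 = 0.64 | 42/67 = 0.63 | 21/46 = 0.46 | 0.63 | 0.78 |
| 50% | 14 | 32 | 14/26 = 0.54 | 42/74 = 0.57 | 14/46 = 0.30 | 0.56 | 0.78 |

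A second assumed base (30% prevalence, sensitivity and specificity 0.80: RP 24, FN 6, FP 14, RN 56) behaves alike. At r = 25%, sensitivity is 18/24 = 0.75, specificity 56/76 = 0.74 and PPV 18/38 = 0.47, down from 24/38 = 0.63.

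**Direction, for the other tools.** Criterion C also scores the neuropsychological opinion, the on-road opinion and the TRIP separately. Suppose one of these was favorable while the opinion that governs support was unfavorable. If support then removes the risk, that tool's case moves from FN to RN. On the first base, moving 3 of the 12 FN gives sensitivity 28/37 = 0.76, specificity 45/63 = 0.71 and NPV 45/54 = 0.83. That tool looks better because another opinion prompted the support.

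**Check of an obvious remedy.** One could drop supported participants and recompute everything. On the first base, excluding half of the test-positives (both cells equally) leaves RP 14, FP 9, FN 12, RN 42. Sensitivity is then 14/26 = 0.54 and specificity 42/51 = 0.82, against 0.70 for both. Only PPV is recovered: 14/23 = 0.61. The exclusion removes almost only test-positives, so it biases both sensitivity and specificity.

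**The case against.** The strongest reply is that the article describes proposals in a non-interventional study. It gives no uptake, no timing of rehabilitation or reassessment relative to months 6 and 12, and no sign of how many reassessed participants resume driving in that window. This stands. A reader might infer that an unfavorable opinion triggers or prescribes rehabilitation and a second assessment; the text supports only that these are among the options offered.

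A reader might also infer that criterion C must understate every assessment. The documents do not support that. The downward shift is assured only for the opinion that governs support, and only where support lowers the reported risk. The outcome is the participant's own perception, and section 3.2 lists greater awareness of one's driving ability among the aspects of the evaluation to be explored. Greater awareness could raise the rating rather than lower it.

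It is tempting to add natural recovery, citing section 3.3: "Although cognitive sequelae may persist for many years after brain injury, they tend to diminish over time". That sentence concerns heterogeneity in time since injury. Recovery would also affect participants with favorable opinions, so it does not simply reinforce the effect.

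A modest shift would be hard to see in the data. With 40 at-risk participants and sensitivity 0.70, the 95% interval is about ±1.96·√(0.70 × 0.30/40) = ±0.14, wider than the loss at r = 10% or 25%. But the interval reflects chance, whereas this shift is systematic and would not shrink with more participants.

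Finally, the case report form is not shown and may already record rehabilitation and reassessment. That affects what must be collected. It does not change Table 4, its cell labels, or the predictive reading in section 3.2, all of which the article fixes.

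**Conclusion.** The concern holds in conditional form. Support offered by index result lies between the opinion and the outcome, and Table 4 scores a flagged risk that support removed as a false positive. For the governing opinion the direction is certain once this happens: sensitivity, specificity, PPV and accuracy fall and NPV stays put. For the other tools the direction is open, so comparisons between tools may be distorted as well.

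The size cannot be derived from the article. Under the assumed first base, the loss in sensitivity and specificity is about 0.02 to 0.03 at a 10% shift and 0.06 to 0.07 at 25%; PPV loses about 0.06 and 0.15. These figures assume that support lowers perceived risk in that share of true positives and changes nothing else.

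This touches one exploratory secondary criterion. The main concordance analysis is unaffected. It is still worth correcting, because it changes what criterion C can be said to show.

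**What to change.** 1. At months 6 and 12, record whether the participant has had driving rehabilitation and/or a new assessment since the index opinion, with date and result, unless the case report form already does so.
2. Keep the all-participant Table 4 as the main table for criterion C.
3. Beside it, show the proportion with increased perceived risk among unfavorable participants (PPV), split by intervening support. Do not compute sensitivity or specificity in a table that leaves out supported participants.
4. State in sections 2.3.2.1 and 3.2 that the all-participant figures describe agreement between the opinion and perceived risk after the support that follows it, not the predictive accuracy of the assessment alone.

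The cost is a few items on questionnaires that are already sent, one additional display and two sentences of text. The split will have small cells and wide intervals, and the supported and unsupported groups are not randomized, so it should be read as descriptive. Nothing in participants' care changes.

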#### Longitudinal study

2.2.2

Six and 12 months after deliberation of the approved doctor’s opinion, the study investigators of the rehabilitation centers will send questionnaires to each participant of the cross-sectional study in order to study the road risk prediction performance of the tools and professional opinions. These questionnaires can also be completed with the help of a third party or a therapist. They will aim to gather information about participants’ driving in the 6 and 12 months since the opinion on fitness to drive was delivered. The elements investigated will concern:- aberrant driving behavior with DBQ validated in French (Guého et al., 2014),- possible changes in driving habits with DHQ, based on the Canadian Jerome Driving Questionnaire (JDQ©), and- road risk (accident rate and perceived risk).

Six months after the approved doctor’s opinion, participants will also be asked to complete a questionnaire (support for resuming driving questionnaire) to assess the relevance of multiprofessional educational support aimed at encouraging them to resume driving or dissuading them from doing so. In order to limit participant drop-outs, if they do not respond within one month, a reminder is sent by their SMR referent, with a one-month response period and this procedure will be repeated a second time if no response is received after this deadline. After these two reminders, the SMR referent may also contact the participant by phone to ensure that the e-mails have been received. If the participant refuses or does not reply, the SMR referent sends a final e-mail to the participant to inform them that they will be excluded from the longitudinal study.

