#### Longitudinal study (secondary evaluation criteria C to E)

2.3.2

Six and 12 months after deliberation of the approved doctor’s opinion, a longitudinal analysis will enable the following secondary objectives to be met:C. Estimate the road risk prediction performance metrics of each assessment tool (cf. main objective) and of the TRIP, as well as of the approved doctor’s opinion;D. Explore participants’ changes in their driving habits;E. Explore the impact of educational support to encourage or dissuade driving resumption (only explored after 6 months).

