##### Secondary criterion E: impact of pedagogical support

2.3.2.3

In the context of pedagogical support, the usefulness of the advice given will be analyzed using a 5-point Likert scale, ranging from “Very useful” to “Not at all useful.” The information can be collected globally, or by type of advice.

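### A therapist from the assessing team may help complete the follow-up forms that supply the reference outcome for objective C, which may bias the predictive metrics in an unknown direction

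*Protocol article*

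**What the plan says.** Protocol article, section 2.2.2 (Longitudinal study): at 6 and 12 months "the study investigators of the rehabilitation centers will send questionnaires to each participant of the cross-sectional study". Their stated purpose is to show how well the tools and the opinions predict road risk. The forms cover the DBQ, the DHQ, accidents and perceived road risk. On completion: "These questionnaires can also be completed with the help of a third party or a therapist". No condition is attached to who the therapist is.

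Section 2.2.1.4 (On-road driving assessment): "A driving instructor and a therapist carry out this 45-min assessment in a dual-control driving school car", and those professionals then give an opinion. Under sections 2.2.1.5, 2.2.1.6 and 2.2.1.8, the center's professionals agree a joint opinion, tell the participant, and offer support or solutions.

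Section 2.3.2.1 (Secondary criterion C) and Table 4 take the participant's own rating of road risk (lower, identical or higher than before the injury) as the reality against which each opinion is scored.

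For criterion E, section 2.3.2 states the aim as "Explore the impact of educational support to encourage or dissuade driving resumption", while section 2.3.2.3 says "the usefulness of the advice given will be analyzed using a 5-point Likert scale".

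**The concern.** A study of predictive performance needs a reference outcome recorded independently of the prediction. Here a therapist who rode in the car, or who shared in the joint opinion, may sit with the participant while perceived road risk is answered. The helper may steer the answer towards the opinion given. The participant may also be reluctant to admit increased risk to someone who ruled on their fitness. Either would move participants between the columns of Table 4 and alter accuracy, sensitivity, specificity and the predictive values.

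The effect could also be uneven. If participants who need help more often have unfavorable opinions, which the article does not say, the two rows of Table 4 would be affected differently. Section 3.2 intends to use these comparisons to call assessments good predictors of road risk, so it matters which answers were given with such help.

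Criterion E raises a separate point of naming. A usefulness rating cannot show whether support led anyone to resume or stop driving.

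**Working it through.** **Could the helper be someone who formed the opinion?** Section 2.2.2 permits a therapist without restriction. The forms are sent by investigators of the assessing centers. Section 2.2.1.4 puts a therapist in the on-road assessment. Under section 2.2.1.3 the occupational therapist already administers the DHQ, DBQ and perceived-risk questions about driving before the injury. A team therapist is therefore allowed and plausible as a helper, though not stated to be the usual one.

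**Which outcomes are touched?** Table 4 uses perceived risk only. Accidents and DBQ answers are on the same forms but do not enter that matrix. The DBQ and DHQ feed criterion D, and section 3.2 mentions accidents as a further correlation.

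**Direction and size.** The article gives no figure to reproduce. The inputs below are assumptions, used only to see how the metrics behave.

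Base case: 100 responders, 30 with increased perceived risk, true Se = Sp = 0.65. Then RP = 30 × 0.65 = 19.5, FN = 10.5, RN = 70 × 0.65 = 45.5, FP = 24.5, and accuracy = (19.5 + 45.5)/100 = 0.650.

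(a) Pull towards the opinion. A share h of answers that disagree with the opinion is changed to agree: RP + h·FP, (1−h)·FP, RN + h·FN, (1−h)·FN.
At h = 10%: RP = 19.5 + 2.45 = 21.95, FN = 9.45, RN = 45.5 + 1.05 = 46.55, FP = 22.05. Se = 21.95/31.40 = 0.699; Sp = 46.55/68.60 = 0.679; accuracy = 68.50/100 = 0.685.

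(b) Uniform under-reporting. A share h of increased-risk answers becomes no increase, whatever the opinion: (1−h)·RP, FP + h·RP, (1−h)·FN, RN + h·FN.
At h = 10%: RP = 17.55, FP = 26.45, FN = 9.45, RN = 46.55. Se = 17.55/27.00 = 0.650; Sp = 46.55/73.00 = 0.638; accuracy = 64.10/100 = 0.641.

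| h | (a) Se / Sp / accuracy | (b) Se / Sp / accuracy |
|---|---|---|
| 0% | 0.650 / 0.650 / 0.650 | 0.650 / 0.650 / 0.650 |
| 5% | 0.675 / 0.664 / 0.667 | 0.650 / 0.644 / 0.646 |
| 10% | 0.699 / 0.679 / 0.685 | 0.650 / 0.638 / 0.641 |
| 20% | 0.744 / 0.708 / 0.720 | 0.650 / 0.626 / 0.632 |
| 30% | 0.785 / 0.739 / 0.755 | 0.650 / 0.616 / 0.623 |

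(c) Uneven help, from a different assumed table: RP = 24, FP = 16, FN = 6, RN = 54. Suppose 50% of the unfavorable and 10% of the favorable group are helped by a team therapist, and half of those helped who have increased risk do not report it. RP loses 24 × 0.5 × 0.5 = 6 to FP, and FN loses 6 × 0.1 × 0.5 = 0.3 to RN. PPV goes from 24/40 = 60% to 18/40 = 45%, Se from 24/30 = 80% to 18/23.7 = 76%, and Sp from 54/70 = 77% to 54.3/76.3 = 71%. With 20% instead of 50% helped, RP loses 2.4 and PPV is 21.6/40 = 54%.

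Mechanism (a) inflates the metrics; (b) and (c) lower some or all of them. The direction is not determined.

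**The case against.** - **The outcome is unblinded whoever helps.** Participants are told the joint opinion (section 2.2.1.6), report the approved doctor's opinion themselves (2.2.1.7) and rate their own risk. Relatives may attend the feedback session, so a relative is not unaware either. This stands: an uninvolved helper removes one avoidable influence and does not blind anything.
- **Help has a purpose.** The test battery was chosen so that people with expressive aphasia or one-sided motor deficits could take part (2.2.1.2). Non-responders leave the longitudinal study (2.2.2) and missing data are not replaced (2.3). A strict ban could lose the most impaired participants. This stands and shapes the fix.
- **The full protocol and case report form are held elsewhere** and may say who helps. That is possible. The point rests on what the article expressly allows, not on a missing detail.
- **Accidents and DBQ answers given to the team might be thought to distort Table 4.** They do not enter it.
- **A reader might infer that advice is rated in front of the adviser.** The support questionnaire is introduced after the sentence on help, in a separate paragraph, and help with it is not stated. That reading is an inference only.
- **Section 3.2 already describes the support questionnaire as self-reported**, with some aspects tied to the fitness decision. This narrows the criterion E point to the word impact and to the absence, in section 2.3.2.3, of any link to driving resumed or stopped.
- **The objectives concerned are secondary, in a study that calls itself exploratory.** This limits the weight of the point.

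**Conclusion.** The concern holds in a limited form. The article permits a clinician who helped form the opinion to help record the outcome against which that opinion is scored. This is an avoidable risk of bias in the objective C metrics. Size and direction cannot be known from the document: with 10% of the relevant answers altered, accuracy moves from 0.650 to 0.685 or to 0.641 depending on the mechanism, and every input to that range is assumed. How often therapists will help, and whether need for help goes with unfavorable opinions, is also unknown.

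A reader might conclude that therapist help is what unblinds the follow-up, or that results will be flattered. The document supports neither. Help is optional, the participant knows the opinion regardless, and plausible mechanisms work in opposite directions.

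Separately, and whoever helps, criterion E as specified measures perceived usefulness and not impact.

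**What to change.** 1. Where help is needed, prefer a relative or a professional who took no part in that participant's assessment, opinion or advice. If none is available, still accept a therapist's help so that the response is not lost.
2. Record on each form who completed it: participant alone, with a relative, with an uninvolved professional, or with a team therapist.
3. Repeat the objective C analysis without forms completed with a team therapist. Those excluded may differ in impairment, so read this as a check on robustness and not as a corrected estimate.
4. Report criterion E as perceived usefulness, by direction of the opinion, beside driving resumption or cessation as far as the month-6 DHQ records it. If help is also given with the support questionnaire, keep the same completion record there.

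Cost: one instruction to centers, one tick-box per form, one extra table, and a small added risk of non-response when another helper has to be found. The completion record should be in place before forms come back, since it may not be recoverable later.
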